#### Depressive and Anxiety Symptoms

The Brief Symptom Inventory [63] will be used to measure the symptoms of anxiety and depression. Six items assess the frequency with which participants felt uncomfortable during the past week because of anxiety symptoms such as “nervousness or shakiness inside” and “feeling tense or keyed up.” An additional 6 items assess the frequency with which participants had felt uncomfortable during the past week because of depressive symptoms such as “feeling blue (or sad)”and “feelings of worthlessness.” Response options range from 1 (not at all) to 5 (extremely).

#### Neighborhood Drug Availability

Neighborhood drug availability [64] will be measured using an adolescent report of 3 items. Adolescents indicate their agreement with each statement on a scale ranging from 1 (strongly disagree) to 5 (strongly agree). Example items include “Marijuana would be easy to find in my neighborhood,” “I know where to get drugs in my neighborhood,” and “Lots of drugs are sold in my neighborhood.” A mean score will be computed such that high scores indicate greater neighborhood drug availability.

#### Neighborhood Resources

Neighborhood physical resources, such as libraries and parks, have been found to contribute to healthy development [64] and play a role in shaping observations and interactions with other residents. Four items asking about the availability or presence of (1) sidewalks or walking paths; (2) parks of playgrounds; (3) recreation, community center, or clubs; and (4) library or bookmobile will be used as indicators of the latent construct of neighborhood resources. Questions will be answered as no (0) or yes (1).

#### Neighborhood Safety

Two questions that ask about (1) feelings of safety in the community or neighborhood and (2) feeling safe at school will be used to indicate this latent construct [65]. These questions will be answered on a 4-point scale, from 1 (never) to 4 (always). Higher scores indicate feelings of safety.

#### Neighborhood Poverty

We will define neighborhood as a geographic unit and will measure it based on the census tract of residence. Census tracts commonly serve as proxies for neighborhoods and are often the basis for geographically delimited resource allocation. Census tract–level data will be acquired on the percentage of residents within each census tract that is at or below the poverty line. Furthermore, mean household income across the census tract will also be gathered as a continuous indicator of neighborhood-level income.

#### Everyday Discrimination

The Expanded Everyday Discrimination Scale [66] is a 10-item measure that will be used to assess the levels of everyday, chronic discrimination. Youth will be asked to identify what they believe to be the main reason or reasons for their experiences (eg, gender, race, and age). Youth will be asked to report on how often any of the following things happen to them (eg, “you are treated with less courtesy than other people are”) on a 5-point Likert scale (1=never and 6=almost every day). Scores on the Expanded Everyday Discrimination Scale range from 10-60, with higher scores indicating higher levels of chronic discrimination.

#### Extracurricular Activity

Youth will be asked to report all of their extracurricular activities from the past year. Specifically, youth will be provided with a list of activities and will be asked to indicate their involvement in these activities. Extracurricular activities were grouped into the following 5 categories based on previous research: school involvement or activities—school band, drama, and dance; team sports; and academic clubs—and community involvement or activities—including church attendance and volunteer and community service type activities. In addition to indicating activities they are involved in, youth will also be asked follow-up questions about each activity [67]. Specifically, they will be asked about (1) the frequency of their participation or involvement ("one day", "two or three days", "four or five days", or "six or seven days"), (2) their enjoyment of these activities ("never", "sometimes", "usually", or "always"), and (3) their length of involvement ("less than one year", "one year", "two or three years", "four or five years", or "six years or more").

## Results

### Overview

A previous analysis from a community-based substance use initiative in Paterson, New Jersey, that the principal investigator was a part of, found that among youth living in the first ward of Paterson (eg, Paterson consists of 6 wards), 1 in 4 youth admitted to using marijuana in the past 30 days [39]. Marijuana is thus the most accessible substance to Paterson youth, followed by alcohol. Paterson residents have extreme access to substances including alcohol because of the high number of alcohol outlets in the city. The factors that make Paterson an important city to study for this project are (1) the significant representation of the 2 largest ethnic groups in the nation (Black and Hispanic) that reside in Paterson and (2) the city’s wide availability of licit and illicit drugs that may impact community norms and values. For example, based on the parameters set by the New Jersey Division of Alcoholic Beverage Control [40], the city of Paterson consists of more than 147,000 residents and should not exceed a total of 49 consumption licenses (restaurants and bars) and 19 off-premises licenses (liquor stores and bodegas). However, Paterson is only 8.4 square miles and has more than 200 alcohol outlets—4 times the legal limit [39]. Alcohol outlet density is not only associated with crime, violence, and heavy alcohol and drug use but also provides the youth in Paterson access to alcohol, leading to underage drinking [41-43]. Among Paterson youth within the first ward, between the ages of 13 and 18 years, 30% of Paterson youth have used alcohol before the age of 13 years [39]. Local-level data show that Paterson youth in the first ward, who drank alcohol during the past 30 days, were also 3 times more likely to smoke marijuana before the age of 14 years [39]. Given the emerging evidence that has been disseminated from this community, it is essential to develop more robust procedures to understand the impact of the environment and neighborhoods on drug use and mental health among Paterson youth.

The study is currently in the first phase of planning and will begin recruitment at the end of year 1 (August 2021) and will complete recruitment at the end of year 3 or when the target number has been reached. By year 4, the pilot intervention will be introduced to the community, and participants will be enrolled to participate. The study is currently under review at the principal investigator’s home institution (Yale University). The study was funded as of September 2020 by the National Institutes of Health Office of the Director. Funding will be completed by August 2025. The results of the study will be published on an ongoing basis.

### Data Analysis Plan

#### Quantitative Data Analysis

We will first discuss common issues that will guide data analysis and then describe the analytical methods specific to the proposed research. We will check for assumption violations by assessing normality, distribution, and collinearity issues. Appropriate variable transformations will be applied to severely nonnormal variables [68]. Multicollinearity will be tested by calculating variance inflation factor and tolerance. We foresee that some data will be missing at random. We will examine patterns and missing variables (ie, completely at random, missing at random, or missing not at random) [68]. Structural equation modeling (SEM) with full information maximum likelihood can account for missing at random [69]. We will perform a sensitivity analysis if there are data missing at random.

#### Outliers

We will be sensitive to outliers in all analyses. Potential problems with outliers will become evident as we compare the results of conventional and robust analyses. We will apply standard methods for outlier detection (eg, analysis of leverage statistics and residuals) and use graphical approaches as well.

#### Statistical Power

In general, statistical power should be adequate. An SEM model with a degree of freedom as low as 20 and a sample size of 300 will have 96% power to build a good-fit model (ie, root mean square error<0.05) [69,70]. With the target sample size (N=720), the study will easily have more df and will achieve higher power to build and test the proposed SEM models. For a multiple regression equation with 5 predictors where the squared multiple correlation is 0.25 and where one wants to detect a predictor that accounts for at least 5% unique variance in the outcome, the required sample size to achieve a power of 0.80 is approximately 115 [68]. As another example, for a logistic regression analysis in which the target predictor is a continuous predictor with 5 other predictors in the equation where the event rate at the mean of all predictors is 0.40 and where the multiple correlation of the predictor with the other predictors is 0.30, the sample size needed to detect an odds ratio (applied to standardized metrics) of 1.75 is 115 [68].

#### Statistical Tests

Owing to the nature of the aims and the hypothesized outcomes, a more advanced and robust test of statistical relationships is needed for this study. SEM is a multivariate statistical analysis technique used to analyze structural relationships using a conceptual model, path diagram, and system of linked regression-style equations. SEM is the combination of factor analysis and multiple regression analysis and is used to capture complex and dynamic relationships between observed and unobserved variables [69,70]. SEM approaches are well-suited for this study because of their ability to deal with latent variables and the assessment of complex mediating relationships in causal analysis. On the basis of hypothesized model mentioned earlier, we predict that neighborhood characteristics will have a direct effect on youth substance use and depressive and anxiety symptoms. These effects will account for youth age (and possibly gender, race, and socioeconomic status). SEM is considered a confirmatory technique, as it extends the possibility of relationships among latent variables and includes 2 components: (1) a measurement model (eg, confirmatory factor analysis) and (2) a structural model. SEM allows the following: (1) more accurate estimates of the effects of hypothesized causal variables, (2) it allows the researcher to estimate all effects simultaneously, (3) greater accuracy of parameter estimates when examining competing models, and (4) it allows the researcher to compare the effects of multiple mediators. To use SEM, there are several assumptions that must be met: (1) a linear relationship is present between endogenous and exogenous variables; (2) there should be a cause-and-effect relationship between the endogenous and exogenous variables that are being tested based on theory; (3) data should be free of outliers because outliers can affect the significance of the model; and (4) there should be a nonspurious relationship between the endogenous and exogenous variables. Nonspurious relationships assume that the relationship between 2 variables cannot be explained without a third variable; (5) equations between variables must be greater than the estimated parameters; (6) a sample of at least 150-200 is preferred with at least 10-15 indicators; (7) error terms among endogenous variables and exogenous variables are assumed to be uncorrelated with other variable error terms; and (8) interval data are to be used for analysis [69,70].

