### Objectives

This study aims to use community-based and innovative methods, such as venue-based sampling and CBPR, to gain a better understanding of the prevalence of substance use and important correlates among youth aged between 13 and 21 years within a lower-income, urban community. Historically, research in this area has focused on individual- and family-level factors that influence youths’ substance use patterns [36]. This protocol will describe the goal of the research; the intended population; and the methods that will be used for sampling, recruitment, and analyses. Specifically, this study will use venue-based sampling and CBPR as a recruitment method to identify vulnerable youth. Specifically, we hope to (1) identify the prevalence of substance use among youth; (2) understand important antecedents and correlates of substance use at the microsystem, exosystem, and macrosystem levels; and (3) use this information to inform social, environmental, and culturally appropriate interventions to address substance use and its correlates among youths in a lower-resourced urban community.

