### Youth Substance Use and Mental Health Trends in Paterson, New Jersey

Local-level data collected by a coalition in Paterson, New Jersey, found that 1 in 4 youth in Paterson used marijuana in the past 30 days [39], indicating that marijuana is the most widely used substance among the youths, followed by alcohol. Compared with other residents in Passaic County, Paterson residents have higher access to alcohol because of the high number of alcohol outlets in the city [39]. Thus, Paterson is a unique city to investigate and uses venue-based sampling techniques for this study because of the following reasons: (1) significant representation of the 2 largest ethnic groups in the nation (Black and Hispanic) that reside in Paterson and (2) the city’s wide availability of licit and illicit drugs that may impact community norms and values. For example, based on the parameters set by the New Jersey Division of Alcoholic Beverage Control [40], the city of Paterson with more than 147,000 residents should not exceed a total of 49 consumption licenses, including restaurants and bars, and 19 off-premises licenses, including liquor stores and bodegas. However, Paterson is only 8.4 square miles and has more than 200 alcohol outlets—4 times the legal limit because of grandfather clauses [37]. Alcohol outlet density is not only associated with increased crime, violence, and heavy alcohol and drug use but also provides Paterson youth with greater access to alcohol, leading to an increased probability of underage drinking [41-43]. Among Paterson youth aged between 13 and 18 years, 30% of youth reported that they had used alcohol before the age of 13 years [39]. Local-level data show that Paterson youth who drank alcohol during the past 30 days were also 3 times more likely to smoke marijuana before the age of 14 years [39]. Of note, 60% of Paterson youth reported purchasing alcohol from liquor stores and 40% of Paterson youth admitted to having an adult purchase alcohol from liquor stores for them [39]. Furthermore, Black (33.3%) and Hispanic (29.7%) Paterson youth reported the highest marijuana use before the age of 13 years [39]. In addition, the city is currently facing an extreme opioid crisis, with Paterson being ranked the second city in New Jersey for the highest rate of heroin abuse [44]. Among Paterson youth, 6.2% reported using cocaine and 6.8% reported using heroin; these rates are higher than the state averages [39]. These findings highlight the need to address substance use among Paterson youth, specifically, investigating antecedents and correlates to inform interventions to reduce substance use among youth. Although empirical studies suggest a bidirectional relationship between substance use and mental health [41], it is important to acknowledge that they are correlated and may influence each other, leading to poorer short- and long-term outcomes. Indeed, among Paterson youth sampled, there is a high mental health burden, as 50% of youth reported experiencing depressive symptoms and 57% reported experiencing anxiety symptoms [39]. Overall, 70% of youth who used either alcohol or marijuana in the past 30 days reported experiencing greater symptoms of anxiety and depression [39]. Given that both depression or anxiety symptoms and substance use are correlated and are associated with other negative health outcomes [45,46], it is important to understand these associations to inform and improve interventions aimed at decreasing mental health disparities and limiting substance use.

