### COVID-19 Contingency Plan

Pending COVID-19 restrictions, we will disseminate the survey on the web and ask youth to identify the venues where they have been in the past 7 days and popular venues where they tend to congregate. After the first wave of participants have identified venues, the research team will visit venues and attempt to recruit additional participants while also observing the surroundings of the selected venues to determine characteristics that can be seen as risky or protective (eg, needles on the ground, number of liquor stores close to the venue, parks, and libraries).

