#### Quantitative Data Collection

For each venue identified, the informants (members from the youth and community advisory board) will provide the name, address, type of venue, and preferred time. Youth and Community Advisory Board members and research staff will visit the venues identified. Parental consent will be requested to be waived because of confidentiality and sensitivity of the study for youth aged <18 years [60]. On agreeing to the study, participants will be asked to complete a brief 15- to 20-minute open survey onsite (eg, using an iPad or paper format version). Participants will also have the opportunity to schedule to complete the survey at a community-based partnering organization and schedule to be a part of the focus group. We will recruit at least 720 youths through venue-based sampling at venues and purposive sampling through community partners (eg, schools and youth-serving organizations) to complete surveys within the first 2 years of the project. The youth will be provided with the survey via a web-based platform. Youth will provide their responses to the survey questions in a secure location. They will be honest with their responses and will have the ability to change or alter previous responses. Surveys will be administered via Qualtrics, a secure survey tool, through the principal investigator’s university license. Questions in Qualtrics will be presented in a randomized format for each participant. Responses will be automatically populated in Qualtrics. The principal investigator will have sole access to the Qualtrics account and will download all the data once we have reached the intended number of participants for the study. Deidentified response data will be stored using a unique code representing each participant. Data will be stored confidentially via the secure databases of principal investigators’ institutions (eg, SPSS [IBM Corporation]). The attribution rate in the study will be operationalized as the number of participants who complete the consent to participate but did not complete the full study. Complete data will be used for the research analysis.

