### Conclusions

This study will have a high impact on prevention research for the following reasons: (1) it targets youth who may be disengaged from services and schools and thus neglected in prevention research; (2) it incorporates an environmental context-sensitive approach to understanding substance use and mental health outcomes; (3) delineates the pathways linking specific contextual factors with the behavioral determinants described in a well-tested theoretical model of social disorganization and socioecological theories; and (4) creates a strong youth and community advisory board with mutual ties among local stakeholders, educators, mental health clinicians, and youth who will be essential to conduct ethical research and to translate the research into a sustainable prevention intervention for youth in Paterson, New Jersey, and urban cities alike. Study findings will have an impact on how substance use and mental health researchers understand how to work with youth and develop programs specifically targeted for them to ensure sustainability.

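### One survey contact per youth cannot support the protocol's causal, mediation and pathway claims, in particular any ordering of substance use and mental health symptoms

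*Protocol article*

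**What the plan says.** **Design.** Under Quantitative Data Collection, "participants will be asked to complete a brief 15- to 20-minute open survey onsite". At least 720 youths are to be recruited "to complete surveys within the first 2 years of the project", which is a window for enrolling youths and not follow-up of each one. The COVID-19 Contingency Plan mentions a wave, but of recruitment: "After the first wave of participants have identified venues, the research team will visit venues and attempt to recruit additional participants". Attrition is defined as "the number of participants who complete the consent to participate but did not complete the full study", with no mention of loss between measurements. The year-4 pilot is a separate enrolment. The article never uses the word cross-sectional; that is inferred from one described contact and no described repeat.

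**Measures.** Use is asked for the past 30 days and for lifetime. Anxiety and depressive symptoms are asked for the past week, which lies inside the 30-day window.

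**Claims.** The Objectives want to "understand important antecedents and correlates of substance use at the microsystem, exosystem, and macrosystem levels". The Procedures overview adds the consequences of use. Statistical Tests predicts a direct effect of neighborhood characteristics on use and on symptoms. It supports SEM by "assessment of complex mediating relationships in causal analysis" and lists comparing several mediators among its advantages. The Conclusions say the study "delineates the pathways linking specific contextual factors with the behavioral determinants".

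**Background.** The section on Paterson trends begins one sentence "Although empirical studies suggest a bidirectional relationship between substance use and mental health" and goes on to say that the two are correlated and may influence each other.

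**The concern.** Mediation and causal claims need an order among the variables. Here exposure, candidate mediator and outcome come from the same questionnaire with overlapping recall periods, and the protocol itself accepts influence in both directions between two of them. Statistical Tests lists a cause-and-effect relation, nonspuriousness and uncorrelated errors as assumptions of SEM. A direction that is assumed cannot also be a result, and uncorrelated errors fit poorly with two variables that may act on each other or share unmeasured causes.

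The findings are meant to inform the adapted prevention intervention. If a significant indirect path from neighborhood through symptoms to use were reported, or the opposite chain, it could be taken as showing what to target, although the survey could not tell the two apart. No passage limits the survey results to association on account of the single time point.

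**Working it through.** No figure in the protocol bears on this point, so there is none to reproduce. The check has two parts.

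**1. Fit cannot choose the direction.** Let X be neighborhood, M symptoms and Y use. Model A is X→M→Y with a direct path X→Y. Model B is X→Y→M with a direct path X→M. Three variables give 3×4/2 = 6 variances and covariances. Each model has 6 parameters (three paths, the variance of X, two residual variances), so df = 6 − 6 = 0. The likelihoods are two factorizations of one joint density:

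f(M|X)·f(Y|X,M) = f(M,Y|X) = f(Y|X)·f(M|X,Y)

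In simulated data sets of 720 the two log-likelihoods never differed by more than 1e-12, which is rounding error.

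**2. How often a wrong-direction chain looks significant.** Inputs: N = 720 (protocol); two-sided 0.05; standardized true paths a and b (assumptions, since the protocol gives none); true chain X→M→Y with no other path. The reversed chain counts as mediation when both of its paths are significant.

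- First reversed path, Y on X: the correlation is ab, and t₁ = ab·√720 / √(1 − a²b²), with √720 = 26.83.
- Second reversed path, M on Y given X: partial correlation r = (b − a·ab) / √[(1 − a²)(1 − a²b²)], and t₂ = r·√720 / √(1 − r²).
- Chance of significance for each: Φ(t − 1.96) + Φ(−t − 1.96). The joint chance is approximated by the product.

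For a = b = 0.3: t₁ = 0.09 × 26.83 / √(1 − 0.0081) = 2.42, chance 0.68. Then r = 0.273 / √(0.91 × 0.9919) = 0.287 and t₂ = 8.05, chance about 1. The product is 0.68.

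| a / b | t₁ | t₂ | Approximation | Simulation |
|---|---|---|---|---|
| 0.1 / 0.1 | 0.27 | 2.68 | 0.058 × 0.765 = 4% | about 5% |
| 0.2 / 0.2 | 1.07 | 5.37 | 19% | 19-20% |
| 0.2 / 0.3 | 1.61 | 8.27 | 36% | 36-37% |
| 0.3 / 0.3 | 2.42 | 8.05 | 68% | 67-70% |
| 0.4 / 0.4 | 4.35 | 10.73 | 99% | 99% |

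The simulation column comes from repeated runs of 2,000 or more samples per setting with the joint-significance test.

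**Two further scenarios** (2,000 samples of 720 each, Sobel test):

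- True order X→Y→M with paths 0.3 and 0.3 plus a direct X→M path of 0.2. Both models were significant in 100% of samples, with mean indirect effects of about 0.09 in each.
- No effect between use and symptoms, only a shared unmeasured cause (0.5 on each, and 0.2 from X to each). Each mediation model was significant in more than 99%.

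A larger sample does not help: t₁ and t₂ both grow with √N, so the wrong chain becomes more often significant.

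**The case against.** The strongest reply is that the plan does not contain the mediation model examined above. The only stated prediction runs from neighborhood to use and to symptoms, side by side. No mediator is named and no path between use and symptoms is drawn. The phrase on causal analysis stands in a general sentence about what SEM can do. This stands. A reader might infer that a use-symptom mediation test is committed to, or that the bidirectionality sentence contradicts the main hypothesis; the document supports neither. But mediation is a stated reason for calling SEM well suited to this study, and an unnamed mediator leaves its direction to be chosen later.

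A reader might also infer that no path in the model can be given a direction. That goes too far. Bidirectionality is stated for use and mental health. One youth's past-week symptoms do not plausibly alter census-tract poverty; there the limits are confounding and residential selection. For self-reported drug availability and safety, reciprocal influence is open, since the Theoretical Framework says individuals also act on their contexts.

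The wording is not uniformly causal: the Abstract speaks of associations. The interviews also ask about the context of initiation, and lifetime use gives some retrospective order. These soften the point, but no past measure of symptoms or neighborhood is described to pair with that history, and Statistical Tests and the Conclusions still go beyond association.

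Finally, zero degrees of freedom belongs to the three-variable illustration, while Statistical Power expects more than 20. Degrees of freedom gained in the measurement part do not settle the arrow: when use and symptoms have the same predictors, reversing it leaves the fit unchanged.

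**Conclusion.** The point holds in a limited form. The protocol claims an inferential property, causal and mediating pathways, that one survey contact does not have, and it states no limit on interpretation. The defect lies in those claims and in any use-symptom mediation analysis run under them. It does not lie in the stated hypothesis of parallel outcomes.

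The equal fit of opposite chains is exact for the just-identified case. The frequency of a wrong-direction finding is illustrative only: about 5% to 99% at N=720 for assumed paths from 0.1/0.1 to 0.4/0.4. The 67-70% at 0.3/0.3 should not be read as the error rate of this plan, because the protocol gives no path sizes and specifies no such model. The conclusion also rests on reading the survey as a single measurement, which every passage on data collection supports but none states outright. No sample size or power figure is affected.

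**What to change.** 1. In Statistical Tests, model substance use and depressive and anxiety symptoms as outcomes of neighborhood with a freely estimated residual correlation and no directed path between them. This agrees with the stated hypothesis and with the acknowledged mutual influence, and it replaces the uncorrelated-error assumption for this pair.
2. Describe survey SEM paths as cross-sectional associations consistent with a prespecified model. Remove or qualify the reference to causal analysis in Statistical Tests, the consequences of use in the Procedures overview, and the delineation of pathways in the Conclusions. Where antecedents remain an aim, say that the survey gives correlates.
3. If any use-symptom mediation model is reported, report the reversed model beside it and draw no directional conclusion.
4. For neighborhood paths, name confounding and residential selection as limits, and reciprocal influence for self-reported drug availability and safety.

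The cost is rewording and one residual correlation in the model. No new data are needed. The downside is a less ambitious claim.
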